### Descriptive analysis

The baseline characteristics will be presented based on different layers of the PaO_2_/FiO_2_ ratio. Quantitative variables will be described using the mean ± standard deviation (M ± SD) or the median quartile interval (median, IQR). Categorical variables will be described in percentages. The significance level was set at 0.05.

### Statistical methods for the primary and secondary outcomes

Analysis of variance will be used for ventilator-free days in 28 days, the number of hours using HFNO, noninvasive ventilation, invasive mechanical ventilation, length of hospitalisation, and hospitalisation cost. When it indicates that at least one group is significant, the Bonferroni correction will be applied.

For the 28-day mortality rate and 28-day intubation rate, we will conduct a survival analysis with the Kaplan-Meier method. We will compare the mortality and intubation rates of the three study groups using a log-rank test. We will use the Cox proportional hazards model to detect the relationship between diagnosis, onset time, PaO_2_/FiO_2_ ratio change, the duration of changing positions, and total position changing time.

Other secondary outcomes, such as the change in the PaO_2_/FiO_2_ ratio, ROX index, Borg scale score within the groups, will be compared with a paired repeated measures analysis of variance or generalised estimating equation based on the integrity of the data. The incidence of adverse events will be analysed using either the chi-square test or Fisher’s exact test. Univariate and multivariate analyses of risk factors for prone position failure will be performed with logistic regression.

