### Study setting

This trial will be conducted in the pulmonary and critical care medicine departments on three campuses of two tertiary A-level teaching hospitals in Chongqing, China, in general wards and the ICUs (The standards for admitting patients to the intensive care unit are shown in Additional file 1). If it is difficult to recruit patients, more departments and hospitals will be involved if they obtain their ethics committee approval.

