### Randomisation and concealment

Two investigators who will not participate in this trial will conduct stratified blocked randomisation. First, they will generate random sequences and blocks of various lengths for different centres and layers with IBM SPSS Statistics 25. Then they will obtain grouping results according to the order of the random numbers in different blocks and layers. Subsequently, the grouping results will be placed in opaque sealed envelopes marked with a serial number for the patients’ enrolment order. In addition, they will have a layer mark for the PaO_2_/FiO_2_ ratio category. The envelopes will then be kept by a person who will not participate in the trial at each centre. The person will only open the corresponding envelope when grouping the patients according to their PaO_2_/FiO_2_ ratio (> 200 mmHg or ≤ 200 mmHg) and their enrolment order.

Due to the nature of the interventions, only data collectors and data analysts will be blinded to each participant’s allocation. They will directly extract data from hospitals’ medical and nursing record systems. For unclear information, they will consult trained clinical staff. These staff are asked not to disclose information about patients’ group allocation or the interventions.

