### Outcomes

#### Primary outcomes

The primary outcome variable is ventilator-free days in 28 days. It is defined as days free from invasive mechanical ventilation or noninvasive ventilation within 28 days after randomisation.

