### Methods for additional analyses

We will conduct subgroup analyses based on the PaO_2_/FiO_2_ ratio (PaO_2_/FiO_2_ > 200 mmHg or ≤ 200 mmHg), time from admission to intervention implementation (< 24 h or ≥ 24 h), position changing time, and different diagnoses. The Bonferroni correction will be used for pairwise comparisons among the three groups. We will handle the missing values of withdrawn patients with the intention-to-treat the analysis and use multiple imputation. We will also do a per-protocol analysis if patients in the supine position group take the intervention that the experimental groups have. Since this is a multicentre study, centre-effect analysis will be implemented.

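### The primary ANOVA and the log-rank tests are described without the centre and PaO2/FiO2 strata used in randomisation; to the extent those strata are prognostic, precision is forgone

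*Protocol article*

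**What the plan says.** Under Randomisation and concealment, the protocol article specifies stratified blocked randomisation. The trial staff preparing it will "generate random sequences and blocks of various lengths for different centres and layers", and on the envelopes "they will have a layer mark for the PaO_2_/FiO_2_ ratio category", the categories being >200 and ≤200 mmHg. Study setting names "three campuses of two tertiary A-level teaching hospitals in Chongqing, China", so there are four or six strata, depending on whether a centre is a hospital or a campus.

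Under Statistical methods for the primary and secondary outcomes, the primary test is given as: "Analysis of variance will be used for ventilator-free days in 28 days". No centre, stratum or covariate term is named. Mortality and intubation are to be compared across the three arms by a log-rank test, again with no mention of strata. The Cox model listed there includes change in PaO2/FiO2, not the baseline stratum.

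The two factors reappear under Methods for additional analyses: "We will conduct subgroup analyses based on the PaO_2_/FiO_2_ ratio" and "Since this is a multicentre study, centre-effect analysis will be implemented". The form of the centre-effect analysis is not given.

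**The concern.** Blocking within strata forces the arms to be nearly balanced on centre and PaO2/FiO2 category. This removes the between-stratum contribution from the true sampling variance of the arm differences. A one-way ANOVA does not know this. Its residual mean square still contains the between-stratum variance, so the estimated standard error exceeds the true one, intervals are too wide and the F test rejects too rarely under the null. Stratification then secures balance, but the gain in precision that could go with it is not collected.

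Baseline PaO2/FiO2 is a plausible predictor of needing ventilation. The investigators treat it as important: they stratify on it, present baseline data by its layers and make it a subgroup factor. At stake is efficiency and a correctly calibrated standard error for the primary comparison, not bias.

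**Working it through.** **Inputs from the protocol article (Sample size).** Mean ventilator-free days 19, 23 and 22; SDs 13, 12 and 11; two-sided alpha 0.05; power 0.80; allocation 1:1:1; 486 analysed (162 per arm).

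**Input not in the documents.** R², the share of within-arm outcome variance explained by the strata. It is assumed to lie between 0.01 and 0.15.

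**Step 1: reproduce the plan's own figure.**
- Error variance: (13² + 12² + 11²)/3 = (169 + 144 + 121)/3 = 144.67.
- Grand mean: 64/3 = 21.33. Sum of squared deviations: 5.44 + 2.78 + 0.44 = 8.67.
- Noncentrality: λ = 162 × 8.67/144.67 = 9.705.
- Critical value of F(2, 483) at 0.05: 3.014.
- Power from the noncentral F: 80.04%. This is reached at 162 per arm, so 486 reproduces exactly as a one-way ANOVA with no covariates.

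**Step 2: the effect of leaving the strata out.** With arms balanced within strata, the true error variance is 144.67 × (1 − R²), while the one-way residual mean square still estimates 144.67. Hence:
- Overstatement of the standard error: 1/√(1 − R²) − 1.
- True type I error of the unadjusted test: P(F(2, 483) > 3.014/(1 − R²)).
- Unadjusted power: the same threshold, with noncentrality 9.705/(1 − R²).
- Adjusted power: noncentrality 9.705/(1 − R²) at the ordinary critical value, with 3 degrees of freedom charged for centre and PaO2/FiO2.

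Worked case, R² = 0.10: standard error 1/√0.90 − 1 = 5.4% too large; threshold 3.014/0.90 = 3.349; type I error 0.036; λ = 9.705/0.90 = 10.78; power 0.807 unadjusted and 0.843 adjusted.

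| Assumed R² | SE overstated by | True type I error, unadjusted | Power, unadjusted | Power, adjusted | Difference (points) |
|---|---|---|---|---|---|
| 0.01 | 0.5% | 0.049 | 0.801 | 0.805 | 0.4 |
| 0.02 | 1.0% | 0.047 | 0.802 | 0.809 | 0.7 |
| 0.05 | 2.6% | 0.043 | 0.804 | 0.822 | 1.8 |
| 0.10 | 5.4% | 0.036 | 0.807 | 0.843 | 3.5 |
| 0.15 | 8.5% | 0.030 | 0.812 | 0.864 | 5.2 |

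**Step 3: simulation check.** With six equal strata balanced by arm, the planned unequal SDs and 6,000 runs per setting, type I error (unadjusted against adjusted) was 4.0% against 4.7% at R² 0.05 and 3.5% against 5.0% at R² 0.10. Power was 77.6% against 79.4%, and 78.8% against 82.7%. Simulated power sits slightly below 80% because the arm SDs differ; at R² 0 it is 78.6% unadjusted and 78.5% adjusted. Direction and approximate size agree with the table.

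**Step 4: how large an R² is plausible?** For an evenly split binary stratum acting alone, a difference d in mean ventilator-free days explains d²/4 of variance, so d = 2√(R² × 144.67). This gives 2.4 days for 1%, 5.4 for 5%, 7.6 for 10% and 9.3 for 15%. The largest treatment effect planned for is 23 − 19 = 4 days. Centre could supply part of the R², but the upper half of the range needs strong strata.

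**The case against.** Four points can fairly be put on the other side.

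- **Silence is not exclusion.** Analysis of variance covers multi-factor models, and the article nowhere calls the test one-way or the log-rank test unstratified. A condensed article may leave the covariate list to a fuller plan that is not shown. Sizing a trial on unadjusted SDs is common and does not fix the analysis model. This stands as far as it goes: one cannot assert that the strata will be left out. What remains is that the only model described has no stratum term, the sample size matches a one-way ANOVA, and both factors are placed under additional analyses.
- **The planned power is not eroded.** A reader might infer that ignoring the strata costs power the trial was counting on. The documents do not support that: 486 was derived from unadjusted SDs and delivers 80.0% with the unadjusted test. What is lost is an available gain.
- **The effect is conditional.** A reader might also infer that the standard errors are simply too large. That depends on R², which no section gives. The entry range is already limited to >100 to ≤300 mmHg, the stratum is a single cut at 200, and the sites are in one city, so a small R² is possible and the effect could be near nil. This stands.
- **Centre is not ignored altogether.** A centre-effect analysis is planned. It has no stated form, however, and is not described as part of the primary test.

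Any error is also in the conservative direction, and the trial calls itself exploratory, which limits the weight of the point.

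**Conclusion.** The point holds in a limited and conditional form. The described primary ANOVA and log-rank tests do not carry the factors by which patients are randomised. If the ANOVA is run one-way and the strata are prognostic, it is conservative and less precise than it need be, by the amounts tabulated. The size rests on an assumed R², on near-perfect balance within strata and on 486 patients analysed; no corresponding figure was computed for the log-rank tests. Type I error does not exceed its nominal level for this reason, and randomisation keeps the comparison unbiased. Confidence is high that the description omits the factors, and moderate at best on how much that matters.

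**What to change.** In the statistical methods section, state that the primary model for ventilator-free days contains arm, centre (saying whether this means hospital or campus, to match the randomisation lists) and PaO2/FiO2 stratum. State that the log-rank tests for 28-day mortality and intubation are stratified by the same factors. Keep the unadjusted ANOVA as a sensitivity analysis. Robust standard errors and use of the continuous baseline PaO2/FiO2 are optional and not needed to resolve the point. If a fuller plan already specifies such a model, a sentence saying so is enough.

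The cost is wording only. Centre and PaO2/FiO2 category must be known before an envelope is opened, so no new data are needed and the sample size need not change. The article reports the trial as still enrolling, with recruitment expected to finish in March 2025; the model should be fixed before any comparison by arm is seen.

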## Background

### Background and rationale

Acute hypoxemic respiratory failure (AHRF) is a group of diseases characterised by acute hypoxemia, increased respiratory drive, and respiratory failure, with a mortality of 40% [1–3]. It is the main cause of hospitalisation and mechanical ventilation in the intensive care unit (ICU) [4]. Helmet noninvasive ventilatory support and high-flow nasal oxygen (HFNO) are the most promising, first-line treatment techniques for mild-to-moderate hypoxemia associated with AHRF [5]. And HFNO is more widely used than helmet noninvasive ventilators [6] because it is well tolerated [7], can reduce lung injury [5], and has a lower treatment failure rate compared to standard oxygen therapy [8]. Despite the benefits mentioned above, HFNO’s failure rate is still as high as 48%, of which the intubation rate is 43%, and the 28-day mortality rate is 19% [6]. How to further decrease its treatment failure rate and increase prognoses in AHRF patients with HFNO therapy has become a more significant question for researchers.

The APP is usually considered the prone position applied to awake patients who have not received endotracheal intubation. It was reported to improve oxygenation and decrease endotracheal intubation rate with minimal costs and side effects [9, 10] in awake patients with AHRF secondary to COVID-19. Better effects were reported on patients whose arterial partial pressure of oxygen to the fraction of inspiration oxygen (PaO_2_/FiO_2_) ratio was < 300 mmHg with noninvasive respiratory support [11–15]. And longer duration is associated with better outcomes [3]. However, the APP is poorly tolerated in patients, and there is a lack of an effective method for improving patient tolerance. The mean tolerance time of most patients is less than 3.5 h [3, 16], which is far less than the recommended 12 h [17, 18]. So, detecting the time-effect relationship of the APP is difficult. So far, meta-analyses on APP have not found any other prognosis-related benefits of APP other than decreasing intubation rate [9, 10]. Whether it can improve patients’ prognoses is still controversial [19]. Patient-centred outcomes like ventilator-free days, hospital length of stay, and mortality are all meaningful outcomes. Moreover, ventilator-free days is an outcome that both doctors and patients care about, as using ventilators can be both expensive and cause some serious side effects [5, 20].

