## Methods

### Trial design

This is a three-arm, parallel-group, multicentre, randomised controlled, open-label exploratory trial. A total of 583 will be randomly assigned to be placed in the semi-recumbent position (control group), the prone position (experimental Group A), and the lateral position (experimental Group B) at a ratio of 1:1:1. The follow-up period was 28 days. We will conduct and report this trial according to Standard Protocol Items: Recommendation for Interventional Trials. The trial design flowchart is detailed in Fig. 1.

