#### Secondary outcomes

28-day intubation rate (intubation is defined as endotracheal intubation and receiving invasive mechanical ventilation);28-day all-cause mortality(defined as death caused by all kinds of diseases within 28 days after randomisation);Change in the daily PaO_2_/FiO_2_ ratio (measured every morning around the same time) during intervention;Change in daily Borg scale score;Daily and total position changing time;Change in daily ROX index: SpO_2_/FiO_2_ to respiratory rate;Number of hours receiving HFNO therapy;Number of hours receiving noninvasive mechanical ventilation and invasive mechanical ventilation;Treatment failure rate (defined as patients who receive noninvasive, invasive ventilation or die after taking assigned positions);The incidence of adverse events;Length of hospital stay and ICU stay.Hospitalisation cost.

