### Data collection and management

The outcomes will be measured during the intervention and 28 days after the patients are enrolled in the group. The data on the duration of different respiratory support, hospital and ICU lengths of stay, and hospitalisation cost will be collected at discharge or the 28th day after enrolment, whichever occurs first. (The data collection schedule is shown in Table 1). Trained nurses will assess the Borg scale score and fill in the bedside inspection forms (Additional file 6) with average vital signs within 3 min at each allotted timepoint and position change time of each round. Supervisors will examine and transcribe inspection forms every day. Two trained researchers who do not know patients’ allocations will check and collect all other data extracted from the electronic medical record system, including data on withdrawn patients. The main researchers will explain every detail of the parts each researcher is responsible for through online or physical training with a set of standard teaching materials, check the training effect through a test, and give one-to-one guidance to every researcher according to their results.

**Table 1 Tab1:** Data collection schedule

Study Period	Timepoint	Assessments
Enrolment	Day 0–1	Eligibility
		Informed consent
Allocation		Baseline information
		PaO_2_/FiO_2_ ratio after receiving HFNO therapy for 2 h
Post-allocation	During interventions (Day 1–termination)	Vital signs
		PaO_2_/FiO_2_ ratio
		Borg scale
		Position changing time (experimental groups only)
		ROX index
		Special treatments
		Respiratory support
		Adverse events
	At discharge/Day 28	Hospitalisation cost
		Number of hours using HFNO
		Number of hours using advanced respiratory support mode
		Number of hours using conventional oxygen therapy
		Length of hospital and ICU stay
Close-out	At Day 28	Death
		Endotracheal intubation

The confidentiality of the data will be preserved when the coded, anonymised data are transmitted and stored at the location of the statistician in charge of the final analysis.

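### Length of hospital stay is compared by ANOVA with no value set for deaths, so an arm with more deaths can appear to have the better (shorter) stay.

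*Protocol article*

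**What the plan says.** The section on statistical methods for the primary and secondary outcomes fixes the test: "Analysis of variance will be used for ventilator-free days in 28 days, the number of hours using HFNO, noninvasive ventilation, invasive mechanical ventilation", and the same sentence continues to "length of hospitalisation, and hospitalisation cost". ICU stay is a secondary outcome but is not in that list.

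The section on data collection and management fixes the cut-off. It covers "The data on the duration of different respiratory support, hospital and ICU lengths of stay, and hospitalisation cost", which "will be collected at discharge or the 28th day after enrolment, whichever occurs first". The trial design section agrees with this: "The follow-up period was 28 days".

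The article does not say how a death enters these outcomes. It gives no assigned value, no restriction to survivors and no competing-risk analysis. Survival methods are named only for mortality and intubation, and multiple imputation is named for withdrawn patients.

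On how common death is, the Background says of HFNO that "the 28-day mortality rate is 19" per cent, and it describes AHRF "with a mortality of 40" per cent.

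**The concern.** A stay can end because the patient went home or because the patient died. ANOVA on days in hospital gives both the same meaning, so a death on day 5 counts the same as a discharge on day 5, and a short stay is normally read as a good one. Applying the same rule in every arm does not protect the comparison, because the number of deaths may differ by arm and the trial sets out to learn whether position changes mortality.

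The Background and the Discussion both name hospital stay, with ventilator-free days and mortality, as a prognostic outcome of interest. A shorter mean stay would therefore be taken as evidence of better prognosis, although part or all of it could come from excess deaths.

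**Working it through.** **The plan's own figure.** The article states no expected value for length of stay. Its only calculated figure is the sample size for ventilator-free days. One-way ANOVA with means 19, 23 and 22, a common SD of √((13² + 12² + 11²)/3) = 12.03 and alpha 0.05 gives 162 per arm, 486 in total, at power 0.800. The figure reproduces, but it has no bearing on this point.

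**Inputs.** From the protocol: 28-day follow-up; 583 patients in three arms, about 194 per arm; mortality of 19% (HFNO, 28 days) and 40% (AHRF). Assumed, because the protocol gives nothing: the underlying hospital stay is the same in all arms and follows a gamma distribution with shape 3 and mean 16 days, cut at day 28; deaths fall evenly over days 0 to 16, so at day 8 on average.

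**Formula.** Let S be the mean stay of survivors after the day 28 cut, D the mean time to death and m the mortality.

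- Mean recorded stay = (1 − m) × S + m × D
- Difference between two arms = (m₁ − m₂) × (D − S)

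When deaths come earlier on average than survivors' discharge (D below S), the arm with more deaths has the shorter mean. For the assumed gamma distribution cut at 28, S = 15.24 days.

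**Results.**

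| Mortality | Mean recorded stay (days) | Difference from 19% |
|---|---|---|
| 19% | 0.81 × 15.24 + 0.19 × 8 = 13.86 | – |
| 29% | 0.71 × 15.24 + 0.29 × 8 = 13.14 | −0.72 |
| 40% | 0.60 × 15.24 + 0.40 × 8 = 12.34 | −1.52 |

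**How often ANOVA would call this significant.** In simulation with 194 per arm, one arm at the higher mortality and the other two at 19%, the test rejects in about 5% of runs when all arms are at 19%, 15% at 29% and 54% at 40%.

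**Sensitivity to the death-time assumption.**

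- With a constant death hazard (the percentage being 28-day mortality if nobody were discharged), the means are 14.2 days at 19%, 13.6 at 29% and 12.9 at 40%. ANOVA rejects in 11% and 40% of runs.
- With gamma death times of mean 9 days, S − D is about 6.25 days. Mortality of 25% against 15% then gives 13.7 against 14.3 days, a difference of 0.6 day. At 19% against 12% the difference is about 0.4 day.

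**Does the day 28 cut do this by itself?** No. With equal mortality in all arms the cut is in place and the means agree (13.9 days in each arm, rejection about 5%). The cut compresses long stays, but the difference comes from deaths.

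**Does the remedy point the right way?** Take the same assumptions, and suppose survivors stay alive and out of hospital from discharge to day 28. Mean days alive and out of hospital, with deaths scored 0, is (1 − m) × (28 − 15.24): 10.3 days at 19%, 9.1 at 29% and 7.7 at 40%. The arm with more deaths now looks worse.

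**The case against.** The strongest reply is that the protocol names only a test, and that the rule for deaths in secondary duration outcomes is commonly left to the analysis plan, which is not shown. That is fair about the missing rule. The choice of ANOVA for length of stay and the end of the count are stated, however, and an analysis plan that follows them with no further rule would carry the bias.

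A second reply is that mortality, intubation and treatment failure are reported separately, so a reader would see the stay beside the deaths. The largest distortion comes with a mortality gap that is hard to miss: 40% against 19% at 194 per arm gives z = 0.21/√((0.40 × 0.60 + 0.19 × 0.81)/194) = 4.7. This limits the harm but does not correct the test. At 29% against 19% the same formula gives z = 2.3, a gap that the trial could well fail to show.

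A reader might infer that the fault extends to the other outcomes in the list. The documents do not support that:

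- **Support hours.** HFNO hours can end with recovery, with escalation or with death. Ventilation hours may even be higher in an arm with more deaths, because deteriorating patients are ventilated before they die while patients who do well contribute zero. These outcomes have no single favourable direction, and that is all that can be said.
- **Cost.** Death ends spending, but care before death may be expensive. The direction is uncertain.
- **The day 28 cut.** This is ordinary administrative censoring at the end of follow-up.
- **ICU stay.** It shares the cut-off but is not assigned to ANOVA, so no stated method is wrong there.

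**Conclusion.** The point holds for length of hospital stay. The stated ANOVA, with a count that death ends and no value for deaths, can favour an arm because more of its patients died. Under the assumptions above the effect is about 0.6 to 0.7 day for 10 points more mortality, and about 1.3 to 1.5 days for 21 points more. The direction needs only that deaths tend to shorten the stay. The size depends on assumed distributions and should not be quoted as a forecast.

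It would go too far to conclude that the trial's main result is at risk or that every duration outcome is biased towards the arm with more deaths. Only secondary outcomes are affected, the trial is labelled exploratory, and the effect is modest at moderate mortality differences. The change is still worth making before analysis, because it is cheap and hospital stay is one of the prognostic outcomes that the article stresses.

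**What to change.** Replace the ANOVA for length of hospitalisation with one of the following, named in advance:

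- time to discharge alive by day 28, with death as a competing event and patients still in hospital censored at day 28; or
- days alive and out of hospital to day 28, with patients who die by day 28 scored 0.

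Use the same approach for ICU stay wherever it is compared between arms.

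Keep the randomised, all-patient comparison of HFNO hours, noninvasive and invasive ventilation hours, and cost. Report each beside 28-day mortality, and state that fewer hours or a lower cost will not be read as benefit on its own. Any split by survival status should be labelled descriptive, because it conditions on something that happens after randomisation.

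The cost is a change of analysis wording. Lengths of stay and death are already on the data collection schedule, and the planned Kaplan-Meier analysis of mortality already needs death times. The downside is that the result for stay is no longer a simple difference in mean days.

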### Objectives and hypothesis

The first objective of this study was to investigate the effects of prone and lateral positions on patients receiving HFNO therapy in terms of ventilator-free days in 28 days and other prognostic factors. The secondary objective is to compare the differences in the impact of the prone and lateral positions on the investigated factors.

The hypothesis of this study is that positioning AHRF patients in the prone position can lead to improved prognoses. Additionally, for awake patients, the lateral position might be more beneficial than the prone position due to its better tolerance.

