### Sample size

We calculated the sample size with NCSS statistical software PASS 2021 (version number: 21.0.3). The estimation of ventilator-free days in 28 days for the control group was 19 days, with a standard deviation of 13, based on what was reported before [29] and the severity of the disease [30, 31]. After being placed in the prone position and lateral position, the ventilator-free days in 28 days are expected to increase to 23 days and 22 days, and a standard deviation of 12 and 11 respectively, according to the mean difference in recent researches [10, 29] and the potential benefits of the refined interventions [16, 32–35]. Using an analysis of variance model with a two-sided alpha level of 0.05 and a power of 0.8. The allocation ratio is 1:1:1, so 486 participants are needed. We estimated a dropout rate of 20% due to poor tolerance and our experience in the pilot trial, so a total of 583 patients will be enrolled.

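### The 80% power belongs to the three-group F test, not to the pairwise objectives, and a closed test would recover part of the pairwise power that gated Bonferroni gives up

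*Protocol article*

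**What the plan says.** The sample size section of the protocol article rests on one power statement: "Using an analysis of variance model with a two-sided alpha level of 0.05 and a power of 0.8". The conclusion drawn from it is "The allocation ratio is 1:1:1, so 486 participants are needed". No power is given for any comparison between two arms.

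The section on objectives and hypothesis asks first what the prone and lateral positions each do to ventilator-free days in 28 days, and second how the two positions differ.

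For the primary outcome, the section on statistical methods prescribes analysis of variance and then: "When it indicates that at least one group is significant, the Bonferroni correction will be applied". It does not count the comparisons. The section on additional analyses does: "The Bonferroni correction will be used for pairwise comparisons among the three groups". Three pairs means 0.05/3 = 0.0167 for each.

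**The concern.** A significant F test says only that the three means are not all equal. The trial's questions are about pairs, and the stated 80% applies to none of them.

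The multiplicity rule then asks each pair to clear two hurdles: the F test at 0.05 and its own test at 0.0167. With three groups the first hurdle already does most of the protecting. If the three means are not all equal, at most one of the three pairwise equalities can be true, so only one false pairwise claim is possible. Dividing alpha by three at that stage guards against errors that cannot occur together.

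Two things are at stake. A reader may take 80% as the chance of detecting the benefit of a position. And the rule costs power, most of all for lateral versus control, without being needed for 5% familywise error.

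**Working it through.** **Inputs**, all from the sample size section. Control: "The estimation of ventilator-free days in 28 days for the control group was 19 days, with a standard deviation of 13". Prone and lateral: "the ventilator-free days in 28 days are expected to increase to 23 days and 22 days", with "a standard deviation of 12 and 11 respectively". Evaluable patients: 486/3 = 162 per arm.

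**1. The protocol's own figure.** Grand mean = (19 + 23 + 22)/3 = 21.33. Sum of squared deviations = 5.444 + 2.778 + 0.444 = 8.667. Mean variance = (169 + 144 + 121)/3 = 144.67, so the SD is 12.03. Noncentrality = 162 × 8.667/144.67 = 9.71. With 2 and 483 degrees of freedom the critical F is 3.014 and power is 80.0%. At 161 per arm it is 79.8%. An SD of 12 also gives 162 per arm (80.2%). So 486 is the sample size of the global F test.

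**2. Pairwise power at 0.0167, before the F gate.** Standard error = √((s₁² + s₂²)/162); critical t = 2.407 on 322 degrees of freedom; power from the noncentral t.

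| Pair | Difference | Standard error | Ratio | Power |
|---|---|---|---|---|
| Prone v control | 4 | √(313/162) = 1.390 | 2.88 | 68.1% |
| Lateral v control | 3 | √(290/162) = 1.338 | 2.24 | 43.6% |
| Prone v lateral | 1 | √(265/162) = 1.279 | 0.78 | 5.4% |

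**3. Power with the gate.** Simulation with normal data, the planning means and SDs, 162 per arm and 400,000 trials. Welch means arm-specific variances; pooled means the analysis-of-variance error term.

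| Rule | Prone v control | Lateral v control | Prone v lateral |
|---|---|---|---|
| F gate, 0.0167, Welch | 68% | 44% | 5% |
| F gate, 0.0167, pooled | 71% | 44% | 4% |
| F gate, 0.05, Welch | 76% | 58% | 12% |
| Welch global gate, 0.05, Welch | 74% | 57% | 12% |

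Under the protocol's rule, 4.5% of trials (Welch) or 2.5% (pooled) have a significant F test and no significant pair. Under the 0.05 rule none did.

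**4. Familywise error of the 0.05 rule.** Every intersection of two pairwise nulls is the global null, so a global test at 0.05 followed by pairs at 0.05 is a closed test. In simulation with SDs 13/12/11 and Welch pairs, the error was 5.0–5.1% when all means were equal. It was 4.9% (control = prone), 5.0% (control = lateral) and 5.0% (prone = lateral) when only one pair was equal. Bonferroni with Welch gives 1.6–1.7% in those last three cases. With the pooled error the closed test reaches about 6% for control versus prone, the two arms with the largest SDs. Arm-specific variances are therefore part of the remedy.

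**5. What the change cannot do.** By the two-sample formula, 80% power at 0.05 without a gate needs about 154, 253 and 2,080 per arm for the three pairs; at 0.0167 it needs 205, 338 and 2,775. The prone–lateral 95% interval has a half-width of 1.96 × 1.279 = 2.5 days, against a planned difference of 1 day.

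**The case against.** Bonferroni after a significant F test is a standard, prespecified procedure that controls familywise error. It is inefficient here, not wrong, and nothing in the protocol contradicts it. The trial calls itself exploratory, and prone versus lateral is its secondary objective, so nothing obliges 80% power for every pair. All of this stands, and it makes the change of rule an improvement, not the correction of an error.

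The powers also depend on the inputs. On a 0–28 scale an arm with mean 23 cannot have an SD above √(23 × 5) = 10.7, yet 12 is assumed for prone. Putting in 10.7 raises prone versus control to 73–75% under Bonferroni and 79–80% under the closed rule. The figures are conditional on the protocol's values, but the pattern does not change.

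Three stronger readings are tempting and not supported:

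- That Bonferroni causes the low power. It explains only part: without it, lateral versus control is still near 58% and prone versus lateral near 12%.
- That a non-significant prone–lateral result will be read as equality. The protocol nowhere says so.
- That the planning means refute the hypothesis. They put lateral one day below prone, while the hypothesis says "the lateral position might be more beneficial than the prone position due to its better tolerance". That wording is hedged, and the tension is a side issue that has no bearing on the multiplicity rule.

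**Conclusion.** The point holds as a mismatch between the stated power and the objectives, together with an avoidable loss of power. The 80% is for the global F test. Under the protocol's rule the pairwise powers are about 68–71%, 44% and 4–5%. The closed test brings them to about 76%, 58% and 12% at 5% familywise error. The gain is largest for lateral versus control, about 15 percentage points.

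This rests on the planning means and SDs, normal data, 162 evaluable patients per arm, exactly three groups, and Bonferroni counted over three pairs. Whether pairs would be tested with pooled or arm-specific variances is not stated, so both are shown.

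**What to change.** - **Statistical methods, and the matching sentence under additional analyses:** for the three-group comparison of ventilator-free days, replace the Bonferroni step. If the global test is significant at 0.05, test each pair at two-sided 0.05 with arm-specific (Welch) variances, as a closed test for three groups.
- **Sample size:** state that 80% power is for the global test, and give the three pairwise powers under the rule adopted.
- **Prone versus lateral:** report it as an estimate with its 95% confidence interval, since neither rule gives it useful power.

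The cost is a few sentences and no patients. Recruitment was still open when the article was published, so the change can be made before analysis. There are two drawbacks: the stated pairwise powers will look less favourable than 80%, and the closed test gives no simultaneous confidence intervals, so the reported intervals should be labelled as unadjusted.
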